### Study Location

Malaysia is the context of this study since it is the host country for many international students coming from different countries. The target participants in this study will be those new international postgraduate students joining Malaysian public universities. The study includes 20 well-known public universities that attract large numbers of new international students who will be screened according to the inclusion criteria.

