### Randomization and Blinding

Prior to randomization, the researcher will start collecting baseline data. This will be followed by assigning the universities as the unit of randomization. Universities will be randomized in order to reduce contamination between groups [73,74]. However, to ensure allocation concealment, the allocation sequence of the universities selected at the previous stage will be assigned to a control group and an intervention group by the ratio 1 to 1. The purpose of this is to ensure that the number of universities allocated to each group will remain approximately equal (see Figure 1 flowchart) [75-77]. This will be achieved by employing a simple randomization procedure. The researcher will use a computer-generated list of random numbers. It is exclusive to the researcher who will allocate the 10 universities to the two groups. In addition, no one in the control groups will know what the experimental groups will be offered. The statistician who will perform the primary analyses will be blinded to group allocation. This study will follow a CONSORT chart [73] as shown in Figure 1 (study flowchart).

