### Statistical Analysis

We will use SPSS Statistics version 25.0 (IBM Corp) to analyze the data. Statistical significance will be considered as a *P* value of less than .05. Analysis of the data will take into account clustering of students within universities. The study will use statistical analyses, including descriptive statistics of the respondents’ sociodemographic characteristics, chi-square test for nonparametric variables, and 2-tailed *t* test for continuous variables, to compare between the control and intervention groups on sociodemographic variables and primary and secondary outcome measures. Complete case analyses, intent-to-treat analyses, and completer status analyses will be conducted according to the initial allocation of universities to either intervention or control groups. In relation to the missing data, we will follow the guidelines for analyzing and reporting cluster RCTs with missing data established by Fiero et al [141] and Díaz et al [142].

The effectiveness of the intervention will be assessed using the generalized estimation equation (GEE). Specifically, the differences in the research hypothesis in terms of students’ acculturative stress, adjustment (sociocultural and phycological), and intention to drop out will be compared at 3 points—time 1 (preintervention), time 2 (immediately postintervention), and time 3 (3-month follow-up)—between and within the intervention and the control groups adjusted for covariate variables. The GEE method was chosen because of its efficiency in appropriately modeling the structure of the correlations of the pre-post repeated measures and its low degree of reliance on the assumption of normality in the distributions of data for the variables in the analysis. Furthermore, in the context of RCT research, multilevel models such as the GEE are the most appropriate model because they permit the estimation of treatment effects (ie, group differences) across multiple time points within a single statistical model [143].

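### GEE is chosen for its fit to repeated measures, but with 10 randomized universities an uncorrected robust test has a type I error near 12%, not 5%

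*Protocol article*

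**What the plan says.** Statistical Analysis in the protocol article names the method: "The effectiveness of the intervention will be assessed using the generalized estimation equation (GEE"). The comparison is between and within groups at three time points, adjusted for covariates, in SPSS 25 with P<.05 as the threshold. The abstract adds 95% confidence intervals.

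The first reason for the choice is "its efficiency in appropriately modeling the structure of the correlations of the pre-post repeated measures". Low reliance on normality is the second. The section also says that, in randomized trials, "multilevel models such as the GEE are the most appropriate model", because group differences at several time points can be estimated in one model.

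On clustering, the same section promises: "Analysis of the data will take into account clustering of students within universities". It does not say at which level the GEE clusters, which variance estimator is used, or which reference distribution gives the P value.

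On the number of clusters, Randomization and Blinding says of the random-number list: "It is exclusive to the researcher who will allocate the 10 universities to the two groups". The universities are to be "assigned to a control group and an intervention group by the ratio 1 to 1", by simple randomization. Study Location, however, says: "The study includes 20 well-known public universities that attract large numbers of new international students".

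**The concern.** The robust (sandwich) variance of GEE is justified when there are many independent clusters. The independent units here are the universities, about 5 per arm. With so few, the uncorrected sandwich variance is biased downward, and a normal or chi-square reference ignores the uncertainty in that variance. Both errors favour declaring an effect.

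The stated rationale does not address this. Correlation between visits is a within-student matter, whereas the precision of the treatment comparison is governed mainly by variation between universities and by their number. Calling GEE a multilevel model also suggests that it resolves the hierarchy by itself. It is a marginal method with one level of clustering and no random effects.

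At stake are the error rate of the primary test on acculturative stress, the coverage of its interval, and the power that the trial can claim.

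**Working it through.** **Plan's own figures.** Inputs from Sample Size: means 2.58 and 2.07 (difference 0.51), SD 1.08, cluster size 40, ICC .05, 20% attrition. Power is not stated; 80% two-sided is assumed because it reproduces the result.
- n per arm = 2 × (1.96 + 0.8416)² × 1.08² / 0.51² = 70.4, so 71. Stated: 71.
- Design effect = 1 + 39 × 0.05 = 2.95; 71 × 2.95 = 209.45. Stated: 209.
- 209 / 0.8 = 261.25. Stated: 261 per arm, 522 in total.

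The figures reproduce, apart from rounding down. They rest on normal quantiles and do not use the number of universities.

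**Type I error with university as the GEE cluster.** Take K equal-sized universities, K/2 per arm, with normally distributed university means. The uncorrected sandwich variance of the difference in arm means is (K − 2)/K times the unbiased pooled variance between universities. So the robust z equals a t variable on K − 2 df times √(K/(K − 2)), and

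error = 2 × P(t on K − 2 df > 1.96 × √((K − 2)/K)).

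- K = 10: 1.96 × √0.8 = 1.753; on 8 df the error is 11.8%, so coverage is about 88%.
- K = 20: 1.96 × √0.9 = 1.859; on 18 df the error is 7.9%.

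Simulation of university means (200,000 runs, ICC .05, 40 or 52 students each) gave 11.6 to 11.7% for 5/5 and 7.9 to 8.0% for 10/10. A t test on university means gave 4.9 to 5.0% for 5/5 and 5.0% for 10/10.

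**Three time points.** An independence GEE with group-by-time terms and university as cluster (10 universities, 42 students each, 4,000 runs) gave 10.6% for the group difference at time 3 and 12.1% for the group-by-time term. The variance split was assumed: university 0.04, university-by-time 0.01, student 0.50, residual 0.45. Repeated visits are covered once university is the cluster; what remains is the small number of clusters.

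**Uneven split.** Unrestricted simple randomization of 10 gives 5/5 with probability 252/1024 = 0.25. The simulated error is 12.5% at 4/6 and about 15.7% at 3/7.

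**Width after correction.** Ratio = (t quantile / 1.96) × √(K/(K − 2)).
- K = 10: (2.306 / 1.96) × √1.25 = 1.32. The change of quantile alone gives 1.18.
- K = 20: 1.13.

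**Choice of correction at 5/5 with equal sizes.**
- Kauermann-Carroll multiplies the variance by 1.25. With t on 8 df the error is 5.0%.
- Mancl-DeRouen multiplies it by 1.25² = 1.5625. With t on 8 df the error is 3.3%, and the interval is (2.306 / 1.96) × 1.25 = 1.47 times as wide.

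**Power at the planning values.** Completers per university = 209 / 5 = 41.8.
- Variance of the difference = 1.08² × (0.05 + 0.95/41.8) × 2/5 = 0.0339, so SE = 0.184.
- 0.51 / 0.184 = 2.77.
- Power by z: Φ(2.77 − 1.96) = 79%.
- Power by noncentral t on 8 df: 68%.

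**The case against.** The strongest reply is that the defect is read from silence. The article nowhere says that the sandwich variance is uncorrected or that the reference is normal, and a condensed article may leave such detail to an analysis plan. This stands in part: the inflation is conditional on no correction being made. It does not dispose of the point. The article fixes the method, software, threshold and rationale, and that rationale is unsuited to a trial of 10 clusters.

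A reader might infer that the GEE will cluster on student, because the rationale speaks of pre-post measures, and that university correlation will be ignored. In the three-time-point simulation that gives about 26% false positives for the time 3 contrast. The document does not support this reading: it promises to account for clustering within universities, and Results commits to reporting ICCs for each outcome. The 26% also depends on the assumed variance split.

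A reader might also say that the error is at least doubled. That holds for 10 universities but not for 20. Ten is the better-fitting figure: 522 / 10 = 52 recruited and about 42 completing per university, near the planned 40, whereas 522 / 20 = 26. Still, the article contradicts itself on the number, so the claim has to stay conditional.

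Finally, low reliance on normality is a legitimate reason to prefer GEE to a mixed model. GEE can stay if its variance and reference distribution are corrected.

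**Conclusion.** The point holds in conditional form. If the GEE is run with university as the cluster and no small-sample correction, the nominal 5% test has a type I error of about 11.8% with 5 universities per arm, and the 95% interval covers about 88%. With 20 universities the error is about 7.9%.

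The exact figures assume equal cluster sizes, equal arms and normal university effects. An uneven split raises the error, and unequal cluster sizes would generally do so too. The power figures assume the planning values and a comparison at one time point without baseline adjustment.

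The documents do not show that clustering will be ignored, nor that a correction has been ruled out.

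**What to change.** - Reconcile the number of universities (10 or 20).
- Name university as the GEE cluster. Specify a Kauermann-Carroll type variance with a t reference on (universities − 2) df, which is 8 for 10 universities. Mancl-DeRouen is not interchangeable with it on the same df, because it over-corrects.
- Alternatives: an analysis of university-level summaries, or a linear mixed model with random effects for university and student and Kenward-Roger df. The mixed model should include a university-by-time term where the contrast is a change over time.
- Optionally add a permutation check over the allocations that the actual randomization allowed. With a fixed 5/5 split there are 252, so the smallest two-sided P is 2/252 = 0.008.
- Replace the statement that GEE is a multilevel model, and base the justification on the number of universities.
- Restate power on the t reference.

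The cost is analysis wording and modest programming, possibly outside the stated software; data collection does not change. With 10 universities, intervals are about 32% wider than under the uncorrected method (13% with 20), and power at the planning values is about 68%, not 79%. The change should be made before outcome data are analysed.

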### Intervention

#### Intervention Development

The intervention is developed based on the acculturation and acculturative stress models integrating with a cognitive behavioral theory with the aim of focusing on cross-cultural sessions and social and behavioral issues in order to improve social and psychological adjustment and reduce acculturative stress and intention to drop out among international students, especially those who have just arrived at the new hosting environment. Most of these models highlight important variables, including acculturation experience, acculturation strategies, and social support, which have an effect on decreasing acculturative stress and a positive impact on the adjustment of students in host cultures [68,85,86]. Therefore, this study developed an intervention that targets individual variables such as acculturation, social support, and coping strategies, as these factors have the potential to mitigate acculturative stress and, consequently, the international students’ adjustment and intention to drop out.

The educational intervention was developed based on previous experimental studies on the implementation of intervention programs such as Excellence in Experiential Learning and Leadership developed by Mak et al [87], a cultural transition course for international students by Brunsting et al [88], a behavioral intervention to improve cross-cultural relationships consistent with the acculturation models developed by Pritchard and Skinner [89], a cognitive behavioral group intervention on acculturation by Pan et al [90], a group psychological intervention to enhance coping and acculturating by Smith and Khawaja [91], and further intervention and support programs aiming to improve international students’ sociocultural and psychological adjustment and reduce their acculturative stress and intention to drop out of the university [92-94]. Taking into consideration the limitations of these previous intervention studies, development of the intervention in this study is based on the creative use of cross-cultural activities in a program, using a clear quantitative evaluation of the effectiveness of the program and including components that directly target international students’ psychological and sociocultural adjustment and acculturative stress. The intervention was also developed based on the results of previous studies.

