### Study Variables and Instruments

This study will use a self-administered questionnaire consisting of 8 sections measuring the sociodemographic, independent, and dependent variables (study outcomes). The questionnaires will be completed at time 1, time 2, and time 3.

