#### Sociodemographic Information Questionnaire

All participants will be asked to provide sociodemographic information including their gender, age, marital status, educational level, duration of stay in Malaysia, country of origin, prior traveling experience, native language, and self-reported proficiency of language. Self-reported proficiency will also be assessed using a composite score from the following questions: (1) What is your present level of English fluency? (2) How comfortable are you communicating in English? (3) How often do you communicate in English? This method of measuring and assessing English language proficiency has been documented previously by several researchers [122-125]. For this study, participants will be asked to rate their perceived proficiency in speaking, understanding, writing, and having a conversation in Malay and English, as language skills are said to enable sojourners to interact with host nationals and engage in interpersonal relationships, which, in turn, influences their adaptation [125,126].

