#### Other Independent Variables and Measurements

This study focuses on other independent variables that directly or indirect affect study outcomes: acculturation, social support, and acculturative stressors.

Acculturation is a process of adaptation or adjustment to a new cultural context that imposes behavioral, cultural, and psychological changes on the individual in an attempt to be in contact with other individuals or even groups coming from diverse cultural backgrounds [65,127]. Participants’ acculturation will be measured using the Acculturation Index (AI) [128]. The AI was adopted from the two-dimensional acculturation model of Berry et al [61]. These two basic dimensions of acculturation are students’ identification with their heritage culture and their relationship with the host culture. The scale comprises 21 cognitive and behavioral items (eg, food, language, recreational activities, social customs, pace of life, religious beliefs). The instrument is intended to identify acculturation strategies used by participants [110,115,128,129]. Participants will be given two questions on their current lifestyles in two cultures: “How similar are your experiences and behaviors to members of your culture of origin?” and “How similar are your experiences and behaviors to members of Malaysian culture?” This instrument makes use of a 5-point, partly anchored, Likert-type scale ranging from 1=not at all similar to 5=very similar. Independent scores for the two dimensions are in the range of 0 and 105, and higher scores are indicative of the participants’ stronger identification with the host culture. In previous studies, internal consistencies and reliabilities were illustrated by Cronbach alphas ranging from .91 to .94 and .89 to .97 for the heritage culture and host culture, respectively. These reliabilities were confirmed by studies using this measure among sojourns from different cultures living in different populations [115,128,129].

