Perceived social support is another dependent variable, defined as the individual’s impression of the available resources that are supportive for them during their experience of stress and symptoms experienced. Social support encompasses three different dimensions: family, friends, and significant others. Whereas family and friends are recognized as self-explanatory, significant others might be a supervisor, peer, colleague, or any other person with whom the stressed person has constant contact [42,132,133]. In this study, the Multidimensional Scale of Perceived Social Support (MSPSS) aims to measure international students’ perceived social support. It was designed and developed by Zimet et al [132] based on adult samples. Several studies have used the MSPSS with the aim of measuring perceived social support across different cultures [119,132,134-136]. It is reported to be a short, clear, and accurate scale that can be used for measuring social support. The MSPSS is also relatively free of the biases of social desirability [137]. Using this scale, respondents select from the 5-point Likert-type scale choices ranging from 1=strongly disagree to 5=strongly agree. In a previous study, the factor loadings of these items were relatively high, and the measure had internal consistencies (Cronbach alphas) of .79, .81, and .82 for family, friend, and significant other support, respectively. In another study in the Malaysian context, internal consistency results were reported of .88, .64, and .87 for family support, friend support, and the availability of a special person [42,109,119].

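### The covariate wording of the effectiveness model leaves room for adjustment on programme targets re-measured after randomization, and the time 1 outcome is used only as a compared time point, not as a covariate.

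*Protocol article*

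**What the plan says.** The protocol article assesses effectiveness with a GEE. Its Statistical Analysis section compares acculturative stress, adjustment and intention to drop out at times 1, 2 and 3 "between and within the intervention and the control groups adjusted for covariate variables". The covariates are not named, and no measurement time is given for them. Time 1 enters as one of the three points compared.

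Four other places bear on this:

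- Other Independent Variables and Measurements names "other independent variables that directly or indirect affect study outcomes: acculturation, social support, and acculturative stressors".
- Intervention Development says the programme "targets individual variables such as acculturation, social support, and coping strategies", because these are expected to lower acculturative stress and, through it, to affect adjustment and intention to drop out.
- Study Variables and Instruments describes one questionnaire that holds the sociodemographic, independent and dependent variables, and says: "The questionnaires will be completed at time 1, time 2, and time 3".
- Further on under Other Independent Variables and Measurements, the text reads "Perceived social support is another dependent variable", although the same subsection has already listed social support as independent.

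**The concern.** Acculturation and social support are, on the protocol's own account, steps on the path from the programme to lower stress. Their values at times 2 and 3 are mediators. If those values enter the effectiveness model, the group contrast no longer measures the whole effect of the programme. It measures what is left after the part running through these variables is held fixed. Aim 3 asks for the effect of the intervention, which is the total effect. With one row per student and visit, as in a repeated-measures GEE, a scale recorded at every visit can easily be entered at its concurrent value, and nothing in the analysis section rules this out.

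The conflicting label on social support matters for the same reason. A baseline covariate, a mediator and an outcome are handled differently, and the text does not settle which it is.

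The second matter is efficiency. Treating the time 1 outcome only as a compared time point leads to a contrast of changes, or to a contrast of follow-up values alone. Using it as a covariate is generally more precise, and precision is scarce with 10 universities.

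**Working it through.** **1. What the text supports.**

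| Variable | Called independent | Named programme target | Re-measured at times 2 and 3 |
|---|---|---|---|
| Acculturation | yes | yes | yes |
| Social support | yes, and later dependent | yes | yes |
| Acculturative stressors | yes | no (only a component of the guiding model) | yes |
| Sociodemographics | listed separately | no | same questionnaire |

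Two of the three non-demographic independent variables are both targeted and re-measured. The analysis section neither includes nor excludes their later values.

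**2. What timing does to the estimate (mechanism only).** The protocol's planning effect is (2.58 − 2.07)/1.08 = 0.51/1.08 = 0.472 SD. The mediated share is not in the document, so one is assumed. Suppose the programme shifts a mediator by 0.4 SD and the outcome falls by 0.4 SD per SD of mediator. The mediated part is 0.4 × 0.4 = 0.16, a share of 0.16/0.472 = 34%, and the remainder is 0.472 − 0.16 = 0.312. In 1000 simulated trials (10 universities of 40 students, ICC .05) the mean estimates were:

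- no covariate: −0.467
- mediator at baseline: −0.467
- mediator after the intervention: −0.307

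Baseline adjustment loses nothing. The loss arises only from post-intervention values, and its size follows from the assumed share.

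**3. What the time 1 outcome is worth as a covariate.** From Sample Size: ICC = .05 and m = 40. Assumed: student-level correlation between time 1 and follow-up rs = 0.5 or 0.7, university-level correlation rc = 0.5 or 0.8, equal variance (set to 1) at both times.

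- Variance of a university mean: V = .05 + .95/40 = 0.07375
- Covariance of the time 1 and follow-up means: C = .05·rc + .02375·rs
- Follow-up-only contrast: proportional to V
- Change contrast: proportional to 2(V − C)
- Time 1 as covariate with slope b: proportional to V(1 + b²) − 2bC, taking b = rs

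| rs | rc | C | Change | Covariate | Cut vs follow-up only | Cut vs change |
|---|---|---|---|---|---|---|
| 0.5 | 0.5 | 0.03688 | 0.07375 | 0.05531 | 25% | 25% |
| 0.5 | 0.8 | 0.05188 | 0.04375 | 0.04031 | 45% | 8% |
| 0.7 | 0.5 | 0.04163 | 0.06425 | 0.05161 | 30% | 20% |
| 0.7 | 0.8 | 0.05663 | 0.03425 | 0.03061 | 58% | 11% |

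First row in full: 0.07375 × 1.25 − 2 × 0.5 × 0.036875 = 0.05531, and 0.05531/0.07375 = 0.75.

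Simulations with 10 universities over the same correlations gave cuts of about 7-25% against the change contrast and 23-59% against the follow-up-only contrast, in line with the formula.

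**4. Effect on the sample size.** None. Under two-sided 5% and an assumed 80% power (not stated in the readable text), 2 × [(1.960 + 0.842) × 1.08/0.51]² = 70.4, hence 71 per arm. Then 71 × 2.95 = 209 and 209/0.8 = 261 per arm, 522 in total, as the protocol has it.

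**The case against.** The strongest reply is that the protocol nowhere says these scales are the GEE covariates. That is correct. A reader might infer from the label of independent variables that acculturation, social support and stressors are the planned covariates and will enter at their concurrent values, so that the analysis will adjust the effect away. The text supports neither step. Sociodemographic variables such as gender, age and country of origin are at least as plausible, and the programme does not change them. A questionnaire given three times is a collection schedule, not a model. The only analytic timing given for the scales is in aim 1, which describes them at baseline, and baseline adjustment is harmless. Stressors are not among the named targets.

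A covariate list is also something an article may leave to the analysis plan. As a complaint that the covariates are unnamed, this would not stand. What stands is narrower: the adjustment rule as worded is open to post-randomization values in a protocol whose own independent variables include declared programme targets, and the document contradicts itself on the role of social support.

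Nor should a definite loss of power be read into this. No mediated share is given, mediator adjustment may also reduce residual variance, and conditioning on a post-randomization variable can bias in either direction when mediator and outcome share causes.

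On time 1, keeping baseline as a repeated outcome is an accepted approach and not an error. The case for using it as a covariate is a gain in precision. On social support, one can call the conflict a slip, since aims and hypotheses never treat it as an outcome. That is probably so, but the two statements still need reconciling.

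**Conclusion.** The point holds as a clarification with a worthwhile improvement attached, not as a demonstrated flaw in the planned analysis. The wording permits adjustment for mediators measured after randomization; it does not prescribe it. If it happened, part of the total effect could be removed, by an amount that cannot be computed from the document. The simulated fall from −0.467 to −0.307 shows the mechanism under one assumed share and is not a prediction.

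The gain from using time 1 as a covariate can be bounded only under assumed correlations: about 7-25% less variance than a change contrast and 23-59% less than a follow-up-only contrast. This rests on the protocol's ICC and cluster size, on correlations that it does not give, and on equal variances at the two times. The contradiction over social support stands whatever covariates are chosen.

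**What to change.** In the Statistical Analysis section:

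1. For the between-group effect, model the time 2 and time 3 outcomes, with the time 1 value of the same outcome as a covariate and not also as an outcome row.
2. Restrict every other covariate to values measured before randomization. Baseline acculturation, social support and stressors may be included if wanted.
3. Keep the time 2 and time 3 values of those three scales out of the effectiveness model, and use them only in a separate mediation analysis.
4. Report the within-group comparison with time 1 separately, since the aims and hypotheses ask for it.

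Under Other Independent Variables and Measurements, give social support one role and use it throughout.

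The cost is a few sentences. All the data are already to be collected, the Randomization and Blinding section has baseline collection starting before allocation, and the sample size does not change.
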